## ***Documentation and Software***

Data preparation and analysis will be performed using

- **python Version 3.8.1**

and the following **packages** and their **dependencies**:

- **pandas version 1.2.4**
- **scikit-learn version 0.24.2**
- **scikit-survival version 0.15.1**
- **TensorFlow version 2.6.0**
- **PyTorch version 1.10**
- **pycox version 0.2.2**

- **R Version 4.1.1**

## **Further analysis**

The whole dataset will be further split into **women and men** and independent models could be trained and tested for each sub-dataset to further examine the different impact of various circulating biomolecules for men and women.

The dataset could also be split into different **age-groups** to better understand the interaction between circulating biomolecules, age and the severity level of heart disease.

There will be additional groups, by kidney function class, symptom class, heart failure (yes/no), comorbidity index (chadsvasc 4 or more compared to chadsvasc 3 or less)

As we are solving two distinct tasks (prediction of the nights spend in hospital and the time to event analysis) that do not only rely on the same dataset but are also likely to be correlated with each other a **Multi-task learning** approach could be interesting. Building ANNs with multiple outputs for classification and regression at the same time are well known. However, combining time-to-event analysis with a regression or classification ML-task seems to be of ongoing research.

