#### **Analysis Population**

The EAST – AFNET 4 study offered all participants participation in a biosample sub-study. Due to regulatory delays, this offer could not be made to the first 399 patients. The analysis population will consist of all patients randomized in the EAST – AFNET 4 trial in whom biosamples were collected.

For comparison of the effect of the randomized intervention, early rhythm control, we will compare intention to treat populations as a primary analysis.

The analysis population will include those patients from the original study who agreed to also contribute to the circulating biomolecules sub-study. These are 1586 patients of which approximately 50% are women and also around 50% received usual care against about 50% that received early treatment.

We will compare clinical characteristics of the sub-study population with the patients not participating in the sub-study to identify potential differences.

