## EAST-AFNET circulating biomolecules sub-study

- **Specific hypotheses.** Based on our biomedical knowledge, we developed specific hypotheses that will be tested in the EAST – AFNET 4 biomarker sub-study. These include the following:
  1. BMP10 concentrations are associated with recurrent AF and affect recurrent AF differentially depending on the use of sodium channel blockers (flecainide, propafenone).
  2. FGF23 concentrations are associated with recurrent AF.
  3. A combination of ANG2, FGF23, and BMP10 predicts recurrent AF better than natriuretic peptides.
  4. ESM1 concentrations are associated with stroke (both prior stroke at baseline and future stroke during FU) and with the composite of stroke and cardiovascular death
  5. The ABC bleeding score is associated with major bleeding
  6. The ABC stroke score is associated with stroke and with the composite of stroke and cardiovascular death
  7. BNP is associated with heart failure hospitalizations and with the composite of death or heart failure hospitalization
  8. Angiotensin 2, FGF23 (alone or in combination or in combination with ESM1) are strong predictors for stroke or stroke and ACS, or stroke + ACS + CV death

- The 14 circulating biomolecules:
  - ANG2
  - BMP10
  - Cancer-Antigen 125 (CA-125)
  - Cardiac C-Reactive Protein High Sensitive
  - Creatinine (enzymatic determination)
  - D-Dimer [Explicit units would be "ug FEU/mL]
  - ESM1
  - FBP3
  - FGF23
  - Growth Differentiation Factor-15
  - Interleukin-6
  - IGFBP7
  - NT-proBNP
  - Troponin T high sensitive (cTnT-hs)

all numeric, continuous scaled

To enable evaluation of these circulating biomolecules in context with clinical information, a list of parameters that are associated with the primary outcome will be included in the analysis. A preliminary list will be taken from the existing analyses in the trial. If there are too many candidates, we will do some variable reduction to discard “redundant” variables without using the association with the endpoints to inform that decision (e. g. correlations, PCA, etc.).

See supplement to the main results publication for a list of preselected parameters.

- additional **clinical** parameters collected at baseline:
  - age
    - numeric, discrete scaled
  - gender
    - categorical, nominal scaled – dichotomous
  - random group
    - categorical, nominal scaled – dichotomous
- BMI
  - numeric, continuous scaled
- Heart Failure, determined using heart failure symptoms and LVEF

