### ***Identification of relevant circulating biomolecules as risk factors***

To identify the circulating biomolecules that can be used as robust explanatory variables i. e. risk factors **permutation feature importance [1]** will be used as it is a model agnostic technique.

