### All variables

A 20 % **hold-out dataset** will be used for evaluating the final model that only relies on the most relevant variables and has been trained on the remaining 80 % of the dataset. At model training time the training set will be further split into **k-fold-cross validation** datasets. The split will be **stratified** for the dependent variable.

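### The SAP wants to know whether biomolecule effects differ by sex and age, but specifies no interaction term or between-group contrast; the only route named is splitting the data, which does not test a difference

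*SAP*

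**What the plan says.** The section Further analysis treats the groups with different degrees of commitment:

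- **Sex.** The split into women and men will be made. Separate models are optional: "independent models could be trained and tested for each sub-dataset to further examine the different impact of various circulating biomolecules for men and women".
- **Age.** A split into age groups is optional and no cut-points are given. The stated aim is "to better understand the interaction between circulating biomolecules, age and the severity level of heart disease".
- **Other factors.** "There will be additional groups, by kidney function class, symptom class, heart failure (yes/no), comorbidity index" (CHA2DS2-VASc 4 or more against 3 or less). No method of comparison is given.

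Elsewhere, the section on identifying relevant biomolecules measures relevance by permutation feature importance, which "will be used as it is a model agnostic technique". Inference Analytics expects the pooled models, which include age and gender, to reflect interactions between clinical parameters and biomolecules. It names no interaction term and no test. The first specific hypothesis supposes that BMP10 acts differently depending on sodium channel blocker use, again without naming a term.

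**The concern.** Whether a biomolecule has a different impact in men and women, or interacts with age, is a question of effect modification. It is answered by an estimate of the difference between the groups, with its uncertainty. Training a model in each group and comparing which markers come out as relevant gives no such estimate. Each group has only part of the events, so a marker with one common effect can rank high in one group and low in the other by chance. Cutting age into groups also discards information within each group.

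The risk is that the sub-study reports sex- or age-specific biomarkers that are products of splitting. A reader of two different importance lists would have no way to tell.

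**Working it through.** The SAP states no power, alpha, event count or effect size for these analyses, so there is no figure to reproduce.

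**Inputs from the SAP**

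- Analysis Population: "These are 1586 patients of which approximately 50% are women", so 1586/2 = 793 per sex.
- "The 14 circulating biomolecules": 14 markers.
- All variables: the final model "has been trained on the remaining 80 % of the dataset". Applied within each sex, which is an assumption, this gives about 634 training and 159 test patients.

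**Assumptions not in the SAP:** event rate 10-25% (79-198 events per sex, 16-40 in each test set), the effect sizes, marker correlation 0.3, and two-sided 0.05.

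**Step 1. One marker, same effect in both sexes.** Power per sex is p = Φ(√D × ln HR − 1.96), with D events per sex and HR per SD. The chance of significance in exactly one sex is 2p(1−p). Example with D = 119 and HR 1.2: √119 × 0.182 = 1.99, so p = Φ(0.03) = 0.51 and 2 × 0.51 × 0.49 = 0.50.

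| HR per SD | 10% (79 events) | 15% (119) | 20% (159) | 25% (198) |
|---|---|---|---|---|
| 1.1 | 0.23 | 0.29 | 0.35 | 0.39 |
| 1.2 | 0.47 | 0.50 | 0.47 | 0.40 |
| 1.3 | 0.46 | 0.30 | 0.16 | 0.08 |
| 1.4 | 0.26 | 0.08 | 0.02 | 0.01 |

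**Step 2. All 14 markers, with permutation importance.** There were 400 simulated data sets per event rate, with 793 patients per sex and the same logistic coefficients in both sexes: nine active markers with odds ratios of 1.1-1.4 per SD and five null. Permutation importance was computed on the test-set AUC after an 80/20 split; significance used all 793 patients per sex. Both sexes used the same model type.

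| Event rate | Markers significant in one sex only (of 14) | At least one such marker | Top-ranked marker differs | Markers shared by the two top-5 lists |
|---|---|---|---|---|
| 10% | 3.66 | 98.3% | 82% | 2.3 |
| 15% | 3.70 | 99.3% | 79% | 2.6 |
| 20% | 3.82 | 99.8% | 79% | 2.6 |
| 25% | 3.76 | 98.5% | 75% | 2.7 |

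Two random lists of five from 14 would share 5 × 5/14 = 1.8 markers on average, so the observed overlap is only modestly better than chance. Among the truly active markers, 35-37% were discordant.

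**Step 3. Direct contrast on the same data.** Testing the difference of the two coefficients, which is equivalent to an interaction term, flagged 5.3-5.6% of markers, close to the nominal 5%.

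**Step 4. Multiplicity.** Over 14 independent tests, the chance of at least one false interaction is 1 − 0.95^14 = 51% (about 54% simulated), and 4.9% at 0.05/14. Six modifiers give 14 × 6 = 84 tests, with 84 × 0.05 = 4.2 false interactions expected and 1 − 0.95^84 = 99% for at least one.

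**Step 5. Can all terms go into one model?** The assumed rates give 1586 × 0.10 = 159 to 1586 × 0.25 = 397 events. With 84 terms that is 159/84 = 1.9 to 397/84 = 4.7 events per interaction term, before main effects. With one modifier it is 159/14 = 11 to 397/14 = 28.

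**The case against.** - **The SAP does not say that differences will be read from separate models instead of interaction terms.** A reader might infer this, but the text does not support it. The sex-specific models and the age split are optional, the other groups come without a method, and nothing rules out an interaction test. This stands: the defect is that no such test is specified.
- **The pooled models may capture interactions.** Inference Analytics makes this an aim, and tree ensembles and networks can do so implicitly. That stands, but it gives no estimate or interval for any particular difference.
- **The SAP states no significance rule per sex.** This also stands, so Step 1 is an analogy. The permutation rankings in Step 2 are closer to the planned output, although they come from a logistic model and not from the planned survival models.
- **A figure of 50% discordance, or seven of 14 markers, is tempting.** At 80% overall power, power per half is Φ(2.80/√2 − 1.96) = 0.51, which gives 50%. But 50% is the maximum of 2p(1−p). At 99% overall power the same formula gives about 24%, and seven of 14 would need every marker to be active at that one power. The documents support neither as a general figure.
- **Women and men might end up with different winning model types.** Between model selection can be read as carrying one selected type forward. The point does not need this argument, since Step 2 used one type for both.
- **Low precision is mainly a matter of sample size.** This is true, and interaction terms do not cure it. They do make it visible.
- **The work is exploratory.** This is true and limits the consequences.

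**Conclusion.** The point holds in limited form. The SAP asks about effect modification by sex, and possibly by age, and lists four further grouping factors, but specifies no interaction term or between-group contrast. Comparing separately trained models does not fill that gap. With identical effects, the simulated top marker differed between the sexes in 75-82% of runs, and about 3.7 of 14 markers were significant in one sex only. A direct contrast kept close to its nominal 5% per marker.

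The sizes rest on the assumed event rates, effect sizes and marker correlation, none of which the SAP gives. They are not uniform: for a single marker with HR 1.4 per SD and event rates of 20-25%, discordance is 1-2%. The main comparison of the 24 pooled models is unaffected.

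**What to change.** Add to Further analysis:

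> Effect modification will be assessed in the pooled Cox and linear regression models by adding biomolecule-by-modifier terms, one modifier at a time: sex, age (continuous), kidney function, symptom class, heart failure and CHA2DS2-VASc. Each interaction estimate will be reported with its 95% confidence interval. Modifiers with several classes will have one joint test per biomolecule. The false-discovery rate will be controlled over the whole set of biomolecule-by-modifier tests. Models trained separately within subgroups are descriptive and will not support a claim of a difference.

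The modifiers should not all enter one model (Step 5), and error control over 14 tests is not enough when at least 84 are made per outcome (Step 4).

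The cost is SAP wording and a few extra regression fits; nothing planned is lost. The downside is imprecision. For a marker-by-sex term the standard error of the log ratio of hazard ratios is about √(2/D). With D = 79 this is 0.16, so the 95% interval spans a factor of exp(1.96 × 0.159) = 1.37 either side of the estimate. With D = 198 it is 0.10 and the factor is 1.22. Only large differences between the sexes could be shown, and the report should say so.
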